### Relevant concomitant care permitted or prohibited during the trial {11d}

Participants will not be restricted from adding eggs or any other food to their diet.

### Provisions for posttrial care {30}

Although the study intervention (egg provision) ends at childbirth, women and infants will continue to engage in the study through 6 months of age. Study staff will conduct follow-up visits at 6 weeks of age and 6-month postpartum to collect additional information on maternal and child health outcomes. The study team intends to seek funding for extended follow-up to track child development up to 2 years of age.

### Outcomes {12}

#### Primary outcome

The primary outcome that will be used to assess the impact of egg supplementation during pregnancy on child malnutrition is newborn birth length, as indicated by LAZ using INTERGROWTH 21st standards.

#### Secondary outcomes

A list of secondary outcomes of the trial can be found in Table 1.

**Table 1 Tab1:** Outcomes of *Deux Oeufs* trial

	**Outcome**	**Type/metric**	**Measurement method**	**Timepoint**	**Aggregation**
***Primary outcome***	Newborn length for age z-score	Continuous (z-score)	INTERGROWTH 21st growth standards	Within 72 h of birth	Mean (SD)
***Secondary outcomes***					
*** Child outcomes***					
* In-utero measurements*	Head circumference z-scores	Continuous (z-score)	INTERGROWTH 21st growth standards	Between 20–26 weeks and 30–34 weeks of gestational ages	Mean (SD)
	Femur length z-scores	Continuous (z-score)	INTERGROWTH 21st growth standards	Between 20–26 weeks and 30–34 weeks of gestational ages	Mean (SD)
	Abdominal circumference z-scores	Continuous (z-score)	INTERGROWTH 21st growth standards	Between 20–26 weeks and 30–34 weeks of gestational ages	Mean (SD)
	Bi-parietal z-scores	Continuous (z-score)	INTERGROWTH 21st growth standards	Between 20–26 weeks and 30–34 weeks of gestational ages	Mean (SD)
	Estimated fetal weight z-scores	Continuous (z-score)	INTERGROWTH 21st growth standards	Between 20–26 weeks and 30–34 weeks of gestational ages	Mean (SD)
	Cerebellar diameter	Continuous (cm)	Ultrasound measurement	Between 20–26 weeks and 30–34 weeks of gestational ages	Mean (SD)
	Corpus callosum length	Continuous (cm)	Ultrasound measurement	Between 20–26 weeks and 30–34 weeks of gestational ages	Mean (SD)
	Thalamus midline axial	Continuous (cm)	Ultrasound measurement	Between 20–26 weeks and 30–34 weeks of gestational ages	Mean (SD)
	Gangliothalamic ovoid diameter	Continuous (cm)	Ultrasound measurement	Between 20–26 weeks and 30–34 weeks of gestational ages	Mean (SD)
	Gangliothalamic ovoid sagittal length	Continuous (cm)	Ultrasound measurement	Between 20–26 weeks and 30–34 weeks of gestational ages	Mean (SD)
	Gangliothalamic ovoid estimated volume	Continuous (cubic cm)	Ultrasound measurement	Between 20–26 weeks and 30–34 weeks of gestational ages	Mean (SD)
* Newborn measurements*	Small for gestational age (SGA) at birth (< 10th percentile and < 3rd percentile)	Binary (two thresholds)	INTERGROWTH 21st growth standards	Within 72 h of birth	Proportion
	Birthweight for gestational age at birth	Continuous (z-score)	INTERGROWTH 21st growth standards	Within 72 h of birth	Mean (SD)
	Preterm live birth (< 37 weeks completed gestation)	Binary	Delivery < 37 + 0 weeks completed gestation	At birth of newborn	Proportion
	Birthweight (g)	Continuous (in g)	Measured using calibrated scale	Within 72 h of birth	Mean (SD)
	Low birthweight	Binary	Birthweight < 2500 g	Within 72 h of birth	Proportion
	Birth weight-for-age z-score	Continuous (z-score)	INTERGROWTH 21st growth standards	Within 72 h of birth	Mean (SD)
	Small vulnerable newborn status	Binary	Any of: SGA (< 10th), preterm (< 37 weeks), or low birthweight (< 2500 g)	Within 72 h of birth	Proportion
	Head circumference z-score	Continuous (z-score)	INTERGROWTH 21st growth standards	Within 72 h of birth	Mean (SD)
* Infant measurements*	Prevalence of stunting among infants	Binary	Length-for-age < −2 SD according to the WHO Multicenter Growth Reference Study standards	At 6 weeks and 6 months of age	Percentage
	Infant weight-for-age z score	Continuous (z-score)	WHO Child Growth Standards	At 6 weeks and 6 months of age	Mean (SD)
	Prevalence of underweight	Binary	Weight-for-age < -2 SD according to the WHO Multicenter Growth Reference Study standards	At 6 weeks and 6 months of age	Percentage
	Child neurodevelopment- HNNE	Continuous/domain score	Hammersmith Neonatal Neurological Examination (HNNE)	At 6 weeks of age	Domain and total scores
	Child neurodevelopment-CREDI	Continuous	Caregiver-Reported Early Childhood Development Instrument (CREDI) score (long form)	At 6 months of age	Domain-specific scores

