*** Other outcomes***					
	Thalamus length, width, and transverse	Continuous (in cm)	Ultrasound measurement	Between 20–26 weeks and 30–34-week gestational ages	Mean (SD)
	Consumption of ASF	Score (0–4)	Based on DQQ questionnaire	Between 9– < 14 weeks, 20–26 weeks, and 30–34 weeks of gestational ages, at time of birth, and at 6-week and 6-month post-birth	Mean (SD)
	Child’s motor, cognitive, socio-emotional, and language development domain specific scores	Domain-specific scores	Based on CREDI long form	6 months of age	Mean (SD)

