### Sample size {14}

Nutritional interventions during pregnancy have yielded mixed results in their impact on LAZ at birth. Previously reported mean difference in LAZ ranges from 0.12 [2, 18] to 0.29 [12, 17]. Notably, the 0.29 effect size observed by Dhaded et al. [12] was associated with nutritional supplementation initiated prior to conception, whereas supplementation beginning in the first trimester yielded a smaller effect size of 0.21. Considering most studies report an effect size below 0.20 and based on the available literature on other food supplementation as found in some literature review papers by Imdad and Bhutta [23] and Stevens et al. [46], we hypothesize a mean difference of 0.18 in LAZ to be both a reasonable and clinically meaningful effect size. As such, we calculate the sample size based on testing two hypotheses simultaneously:$$H0:d1\leq0\;vs.\;Ha:d1>0$$

For our hypothesized effect size, the sample size required with 20% attrition (accounting for pregnancy loss, stillbirths, and loss of follow-up) to attain an 80% marginal power with a 5% level of significance was 478 per arm, based on a two sample one-sided test. Thus, we aim to enroll an overall sample of 956 women in the proposed study. Sample calculation was performed using “pwr” package [5] in RStudio.

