## Statistical methods

### Statistical methods for primary and secondary outcomes {20a}

The primary analysis of the RCT will be based on a modified intention-to-treat (ITT) principle. This trial is designed to formally test the mean difference in the primary outcome of birth LAZ between the treatment arm and the control arm (T1–T2). All women who have a live birth and for whom childbirth length is measured within 72 h will be included in the analysis of the primary outcome. Cases for whom primary outcome data are not available (missing) will not be included in analyses. Descriptive analysis, such as frequency and percentages, will be reported for categorical variables, while means, standard deviation, and quartiles will be reported for continuous variables.

For secondary outcomes, the two-sample *t*-test will be used if the outcome is normally distributed with or without transformation, and the Wilcoxon rank-sum test will be used if the outcome is not normally distributed, where normality will be assessed using the Shapiro–Wilk test and Q-Q plot. Kruskal–Wallis and two-sample rank sum tests will be used if their distribution is non-normal. For both primary and secondary outcomes at birth, exploratory analyses will be conducted using multivariable linear or logistic regression models to adjust for potential confounders (such as baseline SES, gestational age at birth, mother’s education, mother’s age, and dietary diversity) that may be imbalanced across treatment arms. Imbalance of baseline factors may occur as a post-randomization selection bias or by chance alone. Post-randomization selection bias is possible, especially given that participants are not blinded. If this occurs, it will be crucial to adjust for imbalanced confounders in all regression analyses. Village-level heterogeneity will be considered using random effects. Spatial correlation in village-level random effects will be adjusted for if spatial clustering patterns in the outcomes are present. For longitudinal outcomes such as head circumference, linear or generalized linear mixed models will be used to account for heterogeneity in the intercept and slope of growth.

All statistical analyses will be conducted using R and Stata. The statistical significance for regression models will be set at *p* < 0.05 without further adjustment for multiple comparisons.

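### Six secondary fetal brain measures stay in raw units across 6- and 4-week scan windows, and their stated test ignores gestational age at scan, which costs precision

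*Protocol article*

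**What the plan says.** Table 1 (Outcomes {12}, in-utero measurements) lists eleven fetal outcomes. Five of them (head circumference, femur length, abdominal circumference, bi-parietal measure and estimated fetal weight) are INTERGROWTH z-scores. The other six are brain structures in raw units. Five are in cm: "Cerebellar diameter", corpus callosum length, midline axial thalamus, and the diameter and sagittal length of the gangliothalamic ovoid. The sixth, ovoid volume, is in cubic cm. All eleven are measured "Between 20–26 weeks and 30–34 weeks of gestational ages".

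Under the table's other outcomes, "Thalamus length, width, and transverse" adds three measures in cm over the same windows. The Recruitment section gives an approximate appointment date within each window and no target week.

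The statistical methods section {20a} says that, for secondary outcomes, the two-sample t-test "will be used if the outcome is normally distributed with or without transformation"; otherwise the rank-sum test applies. Covariate-adjusted regression is exploratory, is confined to outcomes at birth, and lists gestational age at birth among its covariates. For longitudinal outcomes, with head circumference as the example, "linear or generalized linear mixed models will be used to account for heterogeneity in the intercept and slope of growth".

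**The concern.** Fetal brain structures grow from week to week. If one participant is scanned at 20 weeks and another at 26, part of the difference between their raw measurements is simply age. The plan removes that component for the five neighbouring measures by standardising for gestational age, but not for the six brain measures. The test it states for secondary outcomes does not remove it either.

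In-utero neurodevelopment, judged by ultrasound, is one of the child research questions in Hypotheses and objectives {7}, and these are the brain-specific measures that bear on it. Spread in scan timing adds variance unrelated to treatment, widens the confidence intervals and makes a null result harder to interpret.

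**Working it through.** **Reproducing the plan's own figure.** The document gives no power statement for the brain measures, so the reference is the primary sample size: "we hypothesize a mean difference of 0.18 in LAZ to be both a reasonable and clinically meaningful effect size"; the number "to attain an 80% marginal power with a 5% level of significance was 478 per arm", "based on a two sample one-sided test", with 20% attrition. Taking SD = 1 (not stated, but natural for a z-score):

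- n = 2 × (1.645 + 0.842)² / 0.18² = 382 per arm
- 382 / 0.80 = 477.5, rounded up to 478, which matches.

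**Inputs for the check**

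- From the document: windows of 6 weeks (20–26) and 4 weeks (30–34).
- Borrowed for illustration: 382 per arm and a 0.18 SD effect, both from the primary calculation.
- Assumed: two-sided 5% test, and scan dates uniform within each window.
- Assumed, not in the document: growth per week, g, as a multiple of the SD at fixed gestational age, from 0.3 to 1.0.

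**Formulas**

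- SD of gestational age at scan = width / √12, which is 6/√12 = 1.73 weeks and 4/√12 = 1.15 weeks.
- Variance inflation without gestational age, V = 1 + (g × SD of gestational age)².
- Power = Φ(0.18 / (√V × √(2/382)) − 1.96), where √(2/382) = 0.0724.

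With gestational age in the model, V = 1 and power = Φ(2.488 − 1.96) = 0.70.

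| Window | g | V | Power without gestational age | Equivalent n per arm (382/V) |
|---|---|---|---|---|
| 20–26 weeks | 0.3 | 1.27 | 0.60 | 301 |
| 20–26 weeks | 0.5 | 1.75 | 0.47 | 218 |
| 20–26 weeks | 1.0 | 4.00 | 0.24 | 96 |
| 30–34 weeks | 0.3 | 1.12 | 0.65 | 341 |
| 30–34 weeks | 0.5 | 1.33 | 0.58 | 286 |
| 30–34 weeks | 1.0 | 2.33 | 0.37 | 164 |

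**Sensitivity to scan timing.** If scans cluster mid-window (triangular distribution, SD = width/√24), power is 0.56 and 0.63 in the two windows at g = 0.5, and 0.35 and 0.49 at g = 1.0.

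**Larger effects.** In the 6-week window, a 0.5 SD difference keeps power above 0.99 at g = 0.5 and 0.93 at g = 1.0.

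**Chance imbalance.** The standard error of the between-arm difference in mean gestational age at scan is 1.73 × 0.0724 = 0.125 week in the first window and 1.15 × 0.0724 = 0.08 week in the second.

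**The case against.** The strongest reply is that the plan may already handle this. In the mixed-model sentence head circumference is only an example; all these measures are taken at two visits, and a slope of growth is naturally indexed by age. On that reading only the time axis and the list of outcomes are missing, and a condensed article may leave those to the analysis plan. This stands in part: the text does not settle that gestational age is ignored. But it does state the metric, the windows and an unadjusted test for secondary outcomes, and it does not exempt the brain measures from that test. If the mixed model used visit as its time axis, the spread within each window would remain.

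A second reply concerns scope. The unadjusted test is stated for secondary outcomes, so it reaches six measures. The three listed under other outcomes share the units and windows but have no stated test. That is correct.

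A third is that the size rests on assumptions. The growth rate is not in the document; 0.18 is the hypothesis for length at birth; 382 reflects losses through to birth, not attendance at earlier scans; and the enrolment dating carries some error, so adjustment would not remove all of the age spread. All of this stands, and the figures are illustrative.

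A reader might also infer bias between the arms. The documents do not support that. Both arms have the same visit windows, appointment procedure and reminders, both attend the village site daily, and outcome assessors are to be blinded. Nothing suggests that scan timing would differ by arm.

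**Conclusion.** The point holds as a loss of precision in secondary outcomes. Read as written, the text compares six brain measures by an unadjusted test across windows wide enough for normal growth to add variance. The comparison stays unbiased in expectation under randomisation, and the primary outcome is unaffected.

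The loss runs from slight to severe. Under the stated assumptions, power for 0.18 SD falls from 0.70 to 0.60–0.24 at 20–26 weeks and to 0.65–0.37 at 30–34 weeks, and by less if scans cluster mid-window. A reader might conclude that growth would swamp any arm difference. That goes too far: at the low end of the range the loss is modest, and a 0.5 SD difference remains readily detectable over the growth range used here.

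The change is worth making because the better analysis costs almost nothing, not because the planned comparison is invalid.

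**What to change.** For every ultrasound outcome kept in cm or cubic cm, including the three thalamus measures under other outcomes, replace the unadjusted test with a linear model containing arm and gestational age at scan (linear plus quadratic). Alternatively, state that the planned mixed model covers these measures and uses gestational age at scan, not visit, as its time axis.

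The cost is one sentence in section {20a}. No new data are needed: the five fetal z-scores from the same scans already require gestational age at scan, derived from the enrolment dating.

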## Hypotheses and objectives {7}

The study hypothesizes that women who consume two eggs a day will have children whose LAZ at birth is significantly higher than LAZ among those born to women who consume a typical diet. The typical diet in Rwanda often includes fortified blended flour (FBF), a mixture of corn and soy with added vitamins and minerals, which is commonly provided by the government through various nutrition programs for children, undernourished pregnant women, mothers, and other vulnerable groups. FBF is often shared within the family. Therefore, all pregnant women in the study will receive CSB++ (if not already receiving from the government), and the comparison of the effects of eggs will be over a diet that consumes CSB+. The main objective of the study is to determine whether maternal egg consumption during pregnancy improves a child’s growth, which will be measured at birth, 6 weeks, and 6 months of age. The trial also aims to answer additional research questions related to maternal and child health, including the following:

*Maternal outcomes*
Does maternal egg consumption lead to improved maternal health indicators during pregnancy (including weight gain, blood pressure, anemia, and body mass index (BMI)) when compared to a typical diet?Do women who consume eggs during pregnancy experience reduced levels of anemia following birth compared to those who consume a typical diet?Does maternal egg consumption lead to improved prenatal and postpartum mental health of mothers, when compared to typical diet?

*Child outcomes*

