## Methods: participants, interventions, and outcomes

### Study setting {9}

The study will take place in *Nyagatare* District in the Eastern Province of Rwanda. *Nyagatare* District was selected because it (1) has a relatively high rate of stunting among children under 5 (30%) [33], (2) is within the USAID Feed the Future Zone of Influence, and (3) is not a district or region with the highest rates of malnutrition, where extensive and evolving government and nongovernmental nutritional interventions would challenge operational activities and the interpretability of the study’s findings. Pregnant women living in the catchment areas of *Ndama* Health Center in *Karangazi* sector will be the targeted population. *Ndama* Health Center was purposively selected as the study site because it serves a primarily rural population, and the reported historical number of births within the catchment area will provide a sufficient number of births for the study to meet enrollment targets. The selection of the study site was based on formative field work conducted in collaboration with the University of Rwanda and World Vision Rwanda from July through September 2023 and in concert with local, district, and national health officials.

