At birth, 6 weeks, and 6 months of age, the child’s recumbent length will be measured twice using length boards to the nearest 0.1 cm. Weight will be measured to the nearest 0.1 kg using a digital scale (Seca 334). A third measurement will be taken in case of discrepancies between the first two measurements. For length, a third measurement will be taken if the difference between the first two measurements is more than 0.7 cm. A third weight measurement will be taken in case the difference in weight between the first two measurements is more than 10 g. The two most approximate readings will be averaged for analysis. Head circumference of the infant will be measured to the nearest 0.1 cm using a standard, non-stretchable measuring tape, ensuring accurate and consistent placement around the largest part of the infant’s head (above the eyebrows and ears and around the back of the head) for reliability across measurements. MUAC will also be assessed at 6 months of age using a calibrated, non-stretchable measuring tape placed around the mid-upper arm at the midpoint between the shoulder and elbow, with measurements recorded to the nearest 0.1 cm to monitor nutritional status, and referrals will be made for those classified as moderate or severe acute malnutrition.

Additionally, at 6 weeks of age, infants will be assessed for neurodevelopment using the Hammersmith Neonatal Neurological Examination (HNNE) for newborn development assessment and at 6 months using the Caregiver Reported Early Development Instruments (CREDI), a validated assessment tool [51] used previously in Rwanda [7]. The CREDI (long form) provides domain-specific scores in motor, cognitive, language, and social-emotional development, as well as an overall score. Blood will be drawn from both the mother and the infant at 6 weeks and 6 months and stored as described below. A hair sample from the mother will be requested if consented.

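### After birth, Table 1 compares infant length only as stunted yes/no, which costs roughly 40% to two thirds of the information on length that a continuous LAZ row would keep

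*Protocol article*

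**What the plan says.** Hypotheses and objectives {7} makes the child's growth the main objective, "which will be measured at birth, 6 weeks, and 6 months of age". At birth, length is the primary outcome and is a continuous z-score (Outcomes {12}, Table 1). Sample size {14} is built on the same scale: "we hypothesize a mean difference of 0.18 in LAZ to be both a reasonable and clinically meaningful effect size".

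For 6 weeks and 6 months, the infant part of Table 1 has one length row, "Prevalence of stunting among infants". It is typed as binary, cut at −2 SD on the WHO standards and aggregated as a percentage. Weight at those visits has two rows: "Infant weight-for-age z score" (continuous, mean and SD) and the prevalence of underweight (binary).

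Plans for assessment and collection of outcomes {18a} says that at birth and at both infant visits the child's "recumbent length will be measured twice using length boards to the nearest 0.1 cm".

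Statistical methods {20a} offers mixed models for longitudinal outcomes and gives head circumference as its example. It names neither length nor LAZ after birth.

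**The concern.** The natural follow-up to a birth-length effect is whether it lasts. As Table 1 stands, that question is answered for length only by counting infants below a threshold, so a shift in the whole distribution registers only through those who cross −2 SD. Length is the dimension on which the trial is built, yet it is the one that loses its continuous form after birth. Length-for-age has to be calculated anyway to classify an infant as stunted.

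At stake is the precision of the postnatal length result. A maintained benefit has a materially lower chance of being detected than the same data allow. If a continuous LAZ analysis is added only after results are known, it invites the charge of selective reporting.

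**Working it through.** **Inputs**
- Shift of 0.18 LAZ: Sample size {14}, stated for birth. Carrying it to 6 weeks and 6 months is an assumption.
- Design figures: "to attain an 80% marginal power with a 5% level of significance was 478 per arm, based on a two sample one-sided test", where the 478 is "the sample size required with 20% attrition".
- SD of LAZ: not stated; 1 is assumed and tested in step 1.
- Stunting prevalence: 30% among under-5s in the district (Study setting {9}). None is given for 6 weeks or 6 months, so 20% and 10% are added as assumed values.

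**Step 1: reproduce the plan's figure.** n = 2(1.645 + 0.842)² / 0.18² ≈ 382 per arm, and 382 / 0.8 = 477.5, so 478. This matches with SD 1 and a one-sided test. The two-sided version gives 485, then 607, and does not match.

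**Step 2: power for mean LAZ, 382 per arm.** z = 0.18 / √(2/382) = 2.49. One-sided power is Φ(2.49 − 1.645) = 80%; two-sided power is Φ(2.49 − 1.96) = 70%.

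**Step 3: power for stunted yes/no under the same shift.** With control prevalence p₀, the egg arm has p₁ = Φ(Φ⁻¹(p₀) − 0.18), and z = (p₀ − p₁) / √[(p₀q₀ + p₁q₁)/382]. Worked at 30%: p₁ = Φ(−0.524 − 0.18) = 0.241; z = 0.0594 / √[(0.210 + 0.183)/382] = 1.85. One-sided power is Φ(1.85 − 1.645) = 58%; two-sided power is Φ(1.85 − 1.96) = 46%.

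**Step 4: information lost.** This is measured in two ways:
- (a) For small shifts, the share kept is φ(z_p)² / [p(1 − p)], with z_p = Φ⁻¹(p). At 30% this is 0.348² / 0.21 = 0.576.
- (b) For the 0.18 shift itself, the share kept is the ratio of the n needed for 80% one-sided power. The binary n is [1.645√(2p̄q̄) + 0.842√(p₀q₀ + p₁q₁)]² / (p₀ − p₁)². At 30% the ratio is 382/690 = 0.554.

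| Control stunting | Egg arm | z | Power, one-sided (two-sided) | n per arm for 80%, one-sided | Information lost, (a) / (b) |
|---|---|---|---|---|---|
| 30% | 24.1% | 1.85 | 58% (46%) | 690 | 42% / 45% |
| 20% | 15.4% | 1.69 | 52% (39%) | 831 | 51% / 54% |
| 10% | 7.2% | 1.39 | 40% (28%) | 1233 | 66% / 69% |
| Mean LAZ | – | 2.49 | 80% (70%) | 382 | none |

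The loss reaches one half at a prevalence of about 21% by (a) and about 23% by (b). Even at the most favourable cut, a prevalence of 50%, (a) gives a loss of 36%.

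**The case against.** **Table 1 may not be exhaustive.** Wasting at 6 months and infant head circumference appear in the research questions, and MUAC at 6 months is measured, but none has an infant row in Table 1. The mixed-model sentence in {20a} is open-ended and could take in length, and the full protocol is not shown. This stands as a caution: the article does not forbid a continuous LAZ analysis. But Table 1 fixes the type and aggregation of the postnatal length outcome as binary and a percentage, and nothing in the article commits to more.

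**Stunting is the policy question.** The research questions name stunting, wasting and underweight at 6 months, and the Discussion presents stunting as a national priority. This is a good reason to keep stunting, not a reason to leave LAZ out. These are also unpowered secondary outcomes, which limits how serious the point is.

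**Stronger readings a reader might infer.**
- That at least half the information is lost in every case. At 30%, the only prevalence given, the loss is 42–45%; half requires about 21–23% or less, which is plausible in young infants but undocumented.
- That a maintained effect would probably be reported as no effect. That follows two-sided at all three prevalences. One-sided, power is 52–58% at 20–30%, so detection is slightly more likely than not. The confidence interval for the stunting difference would also show the imprecision.
- That growth information in general is discarded. Continuous weight-for-age is kept at both visits, and the lengths themselves are recorded.

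**Conclusion.** The point holds as a fault in the specified comparison for length after birth. It does not touch the primary outcome, the weight outcomes or the data collected.

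If the planned shift persisted, the binary form would give up roughly 40% to two thirds of the information on length for prevalences from 30% down to 10%. Its power would be 22 to 40 percentage points below that of mean LAZ on the one-sided test, and 24 to 42 points below it two-sided.

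This rests on four assumptions: a 0.18 shift that carries over from the INTERGROWTH scale at birth to the WHO scale in infancy, SD 1, normality, and 382 infants per arm still measured. Further losses by 6 months would lower both sets of powers. The relative loss depends mainly on prevalence and much less on the number retained.

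A change is worthwhile, at modest weight, because the outcome is secondary but sits inside the stated main objective.

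**What to change.** Add one secondary outcome to the infant part of Table 1: infant length-for-age z-score, continuous, WHO standards, at 6 weeks and 6 months, mean (SD). Analyse it as the T1–T2 mean difference with its confidence interval, and keep stunting prevalence beside it. Whether 6-month LAZ should also rank above the other postnatal outcomes is the sponsor's choice; the protocol does not rank its secondary outcomes and this point does not require it.

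The cost is one more secondary outcome and a minor amendment, which {25} says needs approval from both ethics bodies. Outcome lists held elsewhere should be matched if they carry the same gap. No new measurement is needed. Trial status reports enrolment as paused, and {17a} keeps outcome assessors and analysts blinded, so the row can still be added credibly. Because {21b} plans an interim look at secondary outcomes after about 100 births, the amendment should be dated and should state whether any infant length data had been compared by arm.

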### Plans to promote participant retention and complete follow-up {18b}

Study follow-up visits will coincide with participants’ routine visits to the health clinics. Pregnant women in *Nyagatare* District are encouraged to visit health centers every month during their pregnancy. The *Deux Oeufs* study will conduct visits for the trial during two of these scheduled visits at approximately 20–26 weeks and 30–34 weeks of gestation. Participants will also receive a text and phone reminder prior to each visit. The women also visit health clinics at approximately 6 weeks and 6 months after birth for infant vaccination and a well-child exam. The study team will schedule study visits with these routine appointments. Transportation to and from these visits is provided by the study, thus increasing not only retention in the study but also routine ANC and well-child health visits.

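### No stated analysis of HNNE at 6 weeks or CREDI at 6 months allows for the infant's age at testing, which costs some precision on two secondary outcomes

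*Protocol article*

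**What the plan says.** Outcomes {12}, Table 1, lists two developmental tests among the infant measurements:

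- The "Hammersmith Neonatal Neurological Examination (HNNE") at 6 weeks, typed as a continuous or domain score and aggregated as "Domain and total scores".
- The "Caregiver-Reported Early Childhood Development Instrument (CREDI) score (long form") at 6 months, typed as continuous and aggregated as domain-specific scores. It appears again under other outcomes, also without an age reference.

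In the same block, "Infant weight-for-age z score" is typed as a z-score on the WHO standards. Stunting and underweight are binary, but they also name the WHO standards.

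Plans for assessment {18a} says that the CREDI long form "provides domain-specific scores in motor, cognitive, language, and social-emotional development, as well as an overall score". The scale of those scores is not named.

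On timing, the retention section {18b} states: "The women also visit health clinics at approximately 6 weeks and 6 months after birth for infant vaccination and a well-child exam". Study visits are scheduled with these appointments, and no window is stated.

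Statistical methods {20a} says that for secondary outcomes the two-sample t-test "will be used if the outcome is normally distributed with or without transformation", and that "the Wilcoxon rank-sum test will be used if the outcome is not normally distributed". Exploratory regression models are described for outcomes at birth. Mixed models are for longitudinal outcomes.

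**The concern.** Scores on developmental and neurological tests may change with age in the first months of life. This is a general assumption, since the documents do not state it for either instrument. If it holds and the scores are not age-standardised, a spread of ages at a visit adds variation that has nothing to do with the eggs. A t-test or rank-sum test has no means of removing it.

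HNNE and CREDI are the only direct developmental tests behind the neurodevelopment question in Hypotheses and objectives {7}. The other measures named there are ultrasound-based measures and head circumference. What is at stake is precision on that question. Birth length, the primary outcome, is not affected.

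**Working it through.** **The plan's own figure.** Sample size {14} gives a difference of 0.18 LAZ, 80% power, one-sided 5% and 20% attrition. No SD is stated; SD = 1 is assumed here.

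n per arm = 2 × ((1.645 + 0.842) / 0.18)² = 381.6, so 382; 382 / 0.80 = 477.5, so 478. The stated 478 is reproduced. No sample size, SD or power is given for HNNE or CREDI.

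**Which stated analysis reaches these scores.**

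| Analysis in {20a} | Scope | Reaches HNNE and CREDI? | Uses age at testing? |
|---|---|---|---|
| t-test or rank-sum test | Secondary outcomes | Yes | No |
| Exploratory regression | Outcomes at birth | No | Not among the example covariates |
| Mixed models | Longitudinal outcomes | No, each is measured once | Not applicable |

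**Cost as a function of the variance explained by age.** Assumptions: 382 analysed per arm, two-sided 5%, and a true difference detectable with 80% power once age is removed. That difference is (1.960 + 0.842) × √(2/382) = 0.203 SD. If age at testing explains a share R² of the score variance, the variance and the required N rise by 1/(1 − R²), and

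power = Φ(2.802 × √(1 − R²) − 1.960).

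| R² | N multiplier | Detectable difference (SD) | Power |
|---|---|---|---|
| 0 | 1.00 | 0.203 | 80.0% |
| 0.02 | 1.02 | 0.205 | 79.2% |
| 0.05 | 1.05 | 0.208 | 78.0% |
| 0.10 | 1.11 | 0.214 | 75.7% |
| 0.15 | 1.18 | 0.220 | 73.3% |
| 0.20 | 1.25 | 0.227 | 70.7% |
| 0.30 | 1.43 | 0.242 | 65.0% |

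**What R² might be for CREDI.** Let testing ages be uniform over ±w months and let the score rise by b SD per month. Age then adds variance v = b²w²/3, and R² = v/(1 + v). Neither b nor w is in the documents, so both are assumed. Weeks are converted at 4.345 per month.

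| b (SD per month) | Window | R² | Power |
|---|---|---|---|
| 0.1 to 0.5 | ±0.5 month | 0.1% to 2.0% | 80.0% to 79.2% |
| 0.1 to 0.5 | ±1 month | 0.3% to 7.7% | 79.9% to 76.8% |
| 1.11 | ±1 week | 2.1% | 79.1% |
| 1.11 | ±2 weeks | 8.0% | 76.6% |
| 1.11 | ±3 weeks | 16.4% | 72.6% |

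The slope of 1.11 corresponds to a between-child SD of 0.9 months of development (1/0.9).

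**HNNE.** The R² table applies to any score, but no age slope for HNNE at 6 weeks was available. Its row in that table is unknown.

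**Could arms differ in mean age by chance?** With ±3 weeks, the SD of age is 42 days / √12 = 12.1 days. The standard error of the difference between arms is 12.1 × √(2/382) = 0.88 days. A difference of 3 days, for example, would be about 3.4 standard errors.

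**The case against.** **The scores may already be age-standardised.** A reader might infer from the missing z-score label that the arms are compared on raw scores. The article does not say so. It leaves the scale open, and the scoring of an instrument is commonly set in the full protocol or analysis plan. If CREDI is age-standardised, that half of the point falls away. This objection stands, so the point is limited to what the article does fix: the tests it names and the scope of its adjusted models.

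**The comparison may be biased.** A reader might also infer that an arm tested a few days later would show a false developmental advantage. The documents give no mechanism for that. Both arms share the visit schedule, reminders, transport and visit compensation, and egg provision ends at childbirth. Chance would rarely produce a gap of several days, and ordinary chance imbalance is already covered by the standard error of the test. The bias reading is not supported.

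**An unadjusted comparison of randomised arms is valid.** It is, and adjustment here is a choice about efficiency. The choice is still worth making, because exact age is a plausible predictor of a developmental score and costs nothing to use.

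**The size rests on assumptions.** It does. Slopes of 0.1 to 0.5 SD per month give small losses, and only steep slopes with wide windows give material ones. With no stated window, the document does not exclude the material end.

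**Conclusion.** The point holds as one of minor to modest severity on two secondary outcomes. The article does not state that HNNE or CREDI is age-standardised, sets no testing window, and names only tests that cannot allow for age. To the extent that the scores depend on age and are not standardised, age spread is left in the error term.

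The loss cannot be computed from the document. Under the assumptions shown, it runs from under 1 to about 3 power points with a narrow window or a shallow slope. It reaches about 7 to 9 points if age explains 15 to 20% of the score variance, and would be larger beyond that. The slope and window figures apply to CREDI; HNNE remains unquantified. The validity of the comparison and the 478 per arm are unaffected.

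**What to change.** In Statistical methods {20a}, specify that arms are compared on HNNE and on CREDI by linear regression on arm, with exact postnatal age at assessment and randomisation stratum (gestational age group at enrolment) as covariates. For CREDI, age-standardised scores are an alternative. State the score scale in Table 1 in either case.

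Use postnatal age as the age covariate and leave gestational age at birth out of this model. Gestational age at birth may itself be affected by the intervention.

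Report age at assessment by arm for both visits, so that readers can see the spread and check that timing was similar.

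The cost is a sentence or two in the protocol or analysis plan. Birth and visit dates are already needed for the weight-for-age z-scores at the same visits, so no new data are required and the sample size does not change.
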